**Data management and analysis.**

Descriptive statistics will be performed by tabulation of the summary means of the individual condition levels and baseline social demographic characteristics of the children and their caregivers. Participants’ characteristics will be presented in frequency tables. A two-way analysis of variance (ANOVA) will be performed to test the independent main effects of PD and PFT, and the effect of interaction of both PD and PFT. Factor levels will be compared by a pairwise comparison of treatment means (standard error of a difference) or a fisher’s least significant difference (LSD) test. This analysis will be done in both intention to-treat and per-protocol assumptions. All analysis will be expressed in 95% two sided confidence intervals and a p-value of <0.05 will indicate statistical significance.

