**Positive deviance nutrition rehabilitation intervention:**

The PD-program will run for 3-months with 2 weeks sessions (12 days) conducted in each month. Each day sessions will include a half hour education session and a one and half hour peer led cooking session. Education sessions will be introduced through situational discussions and illustrated by an educational medium such as an appropriate game or a message. Caretakers will learn how to rehabilitate their malnourished children under the supervision and the support of positive deviant caregivers. Children will be nutritionally assessed by trained nutrition assistants or clinician on the 1^st^, 6^th^, and 12^th^ day of the sessions and after three months.

Caregivers will learn how to prepare nutrient-rich meals for their children from locally available food identified during the PD-inquiry, and good feeding and hygiene practices. Caregivers will together prepare their own food menus based on the PD-inquiry good foods or what they can conveniently access but of equal nutritional value. The menus will include foods which are locally available and affordable and of balanced nutrient value. Food menus will be repeated at least twice within each monthly sessions. However, because the participating children in the PD program are malnourished, total calorie and protein intake in the menus will exceed the daily normal requirement. For sustainability, participating caregivers will contribute the foods and required ingredients during the sessions from those locally available. Caregivers will also learn how to be able to identify child malnutrition through clinical signs, and other common preventable illnesses in childhood. Names and anthropometric data from the sessions will be recorded so as to track changes in nutritional status[^6^](#_ENREF_6)^,^ [^7^](#_ENREF_7).

1. **Parent facilitator trainings.**

The Parent facilitator training (PFT) intervention is part of the wider CURIE community-based intervention study among children with CP at the IM-HDSS. The CURIE intervention study consists of an intervention and control group (1:1 ratio) selected from a previous cohort of surviving children with CP recruited in the CURIE follow-up study and other eligible children with CP selected from the Iganga Mayuge districts CBOs to make-up the desired sample size of 90 children with 45 children per arm. Ethical approval of the CURIE intervention study has been obtained at reference (SS 5173)

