The parent facilitator training programme is based on the Malamulele Onward Carer-2-Carer program (https://www.malamuleleonward.org/online-resources/c2c-materials) in South Africa. The program is designed to be delivered by parents/caregivers of children with CP in seven workshops that aim to improve CP child’s participation and activities of daily living (e.g, eating, dressing, and play).

**Training parent facilitators**: Four primary caregivers of children with CP from Iganga are trained as parent facilitators by physical therapist. The training involves four weeks of training from a master trainer from Malamulele Onward, herself a parent of a child with CP. Each workshop is approximately two hours long and includes between 6-10 caregivers. Each workshop is led by two parent facilitators who work as a team. To ensure quality and consistency of the workshops, the Parent Facilitators follow a detailed manual adapted from the Malamulele Onward Carer-2-Carer Programme translated into *Lusoga*, the local language. For each workshop the Parent Facilitators have a workshop kit, which includes display materials. No therapist will be involved in the monthly parent-led workshops. Two weeks after the workshops, caregivers and their children will attend a therapist-led practical group session which will have the same theme as the parent-led workshop.

**Parent facilitator-led sessions:** Parent facilitator sessions are held at a convenient community center. At the start of parent facilitator led sessions, caregivers are given a pretest on their knowledge about CP and caring for a child with CP including basic nutrition knowledge. A similar post –test assessment will be done at the end of the training program. Parent facilitator trainings involve 7 sessions that expose caregivers to understanding CP and how to improve body functioning: session1: what is CP? session2: CP as a way of life, Session 3: Getting my child’s body ready to move, Session 4: Eating and drinking a healthy diet, Session 5: communication, Session 6: Play, and Session 7: Central visual impairment. The therapists conduct regular monitoring and evaluation site visits to rural communities where the parent facilitators are working for ongoing training and up-skilling[^19^](#_ENREF_19).

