**b). Physical Distancing**

i). A distance of a minimum of two (2) meters should be ensured during research procedures and activities to prevent person- to- person spread of the Corona Virus.

ii). No more than ten (10) people should converge in one place to undertake research

procedures. It is recommended that research teams ensure at least two (2) square meters

for each person. Research teams should avoid hand-shakes and hugging at all times.

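### Both interventions are delivered in caregiver groups, but the planned two-way ANOVA assumes independent errors; if weight gains correlate within session groups, confidence intervals are too narrow and the 5% level is exceeded.

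*Protocol*

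**What the plan says.** The Data management and analysis section fixes the model: "A two-way analysis of variance (ANOVA) will be performed to test the independent main effects of PD and PFT", together with the interaction of the two. It adds pairwise or LSD comparisons of conditions and sets the inferential standard: "All analysis will be expressed in 95% two sided confidence intervals and a p-value of <0.05 will indicate statistical significance". No session-group, workshop or village term is named. The Sample size estimation section sizes the trial for individual randomization, without a design effect.

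The Interventions section describes group delivery of both factors. For PD: "Each day sessions will include a half hour education session and a one and half hour peer led cooking session". Menus are joint work: "Caregivers will together prepare their own food menus based on the PD-inquiry good foods". PD sessions run on 12 days in each of three months. The number of caregivers per PD session group is not stated. For PFT: "Each workshop is approximately two hours long and includes between 6-10 caregivers", and "Each workshop is led by two parent facilitators who work as a team"; four facilitators are trained in all.

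The Study strengths and limitations section mentions adjustment for baseline factors. That is the only adjustment described anywhere in the protocol.

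**The concern.** Caregivers in one PD session group cook from the same menus, use the same contributed foods and learn from the same positive deviant caregivers. Caregivers in one PFT workshop share its facilitators and discussion. These shared exposures act on weight gain, which is the primary outcome. Children in one group may therefore gain more alike than children in different groups.

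Randomising individuals to PD within each CURIE arm does not remove this. Randomisation balances what existed before allocation, whereas the session group creates its correlation afterwards and only among children who attend. Adjusting for baseline factors does not absorb it either.

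The ANOVA error term would then understate the sampling variance of the factor contrasts. At stake are the p-values and intervals behind the trial's main conclusions on PD and on the interaction, and in part those on PFT.

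**Working it through.** **The plan's own figure.** The precision formula for a main effect uses error variance 8.0, interval width 2.0 and contrast coefficients ±0.5. It gives n = 4 × 8.0 × (4 × 0.25) × (1.96/2.0)² = 30.7, so 31 per cell. The two-proportions calculation (64% vs 29%, two-sided 0.05, power 0.80, pooled, no continuity correction) also gives 31 per arm, 62 in total. Both reproduce, and both treat participants as independent.

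**Inputs for the check.**
- Four cells of 31, two-sided 5% (from the protocol).
- Group size m = 6-10. This is the stated PFT workshop size and is assumed for PD. The COVID-19 plan's limit ("No more than ten (10) people should converge in one place to undertake" research procedures) is consistent with it but does not establish it.
- ICC ρ = 0.01, 0.05 and 0.10, assumed because the protocol gives none.

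**Formulas.** The design effect is DE = 1 + (m − 1)ρ. If the true variance of a contrast is R times what the ANOVA assumes, the actual two-sided error is 2 × [1 − Φ(1.96/√R)].

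*Case A: only PD grouping bears on the PD contrast.* Either only PD children are grouped, or PFT workshops mix PD and non-PD caregivers so that workshop effects largely cancel between PD levels. Half the children carry DE and half carry 1, so R = (DE + 1)/2.

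*Case B: PD and PFT groups are formed separately within each condition.* The variances of the cell means (× 31) are:
- both interventions: (1 − ρ) + 2ρm
- PD only: (1 − ρ) + ρm
- PFT only: (1 − ρ) + ρm
- neither: 1 − ρ

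Their average is 1 − ρ + ρm = DE. The average per-child variance is 1, so R = DE even though the control cell has no groups.

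| m | ρ | DE | Case A: R, error | Case B: R, error |
|---|---|---|---|---|
| 6 | 0.01 | 1.05 | 1.025, 5.3% | 1.05, 5.6% |
| 10 | 0.01 | 1.09 | 1.045, 5.5% | 1.09, 6.0% |
| 6 | 0.05 | 1.25 | 1.125, 6.5% | 1.25, 8.0% |
| 8 | 0.05 | 1.35 | 1.175, 7.1% | 1.35, 9.2% |
| 10 | 0.05 | 1.45 | 1.225, 7.7% | 1.45, 10.4% |
| 6 | 0.10 | 1.50 | 1.25, 8.0% | 1.50, 11.0% |
| 10 | 0.10 | 1.90 | 1.45, 10.4% | 1.90, 15.5% |

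**Simulation.** The 4 × 31 two-way ANOVA was simulated under the null, with 8000 runs per setting. The PD main effect rejected in 4.7-5.2% of runs at ICC 0. With workshops mixing PD levels (Case A) it rejected in 6.6-8.0% at ICC 0.05 and 7.8-10.2% at 0.10. With separate groups per condition (Case B) the figures were 8.0-10.4% and 11.4-16.5%. The top value lies slightly above the formula partly because 31 children split into three groups makes groups of 10.3. The interaction test was inflated to a similar degree as PD in each case.

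**In the plan's own units.** For m = 8 and ICC 0.05, an interval planned at width 2.0 should be 2.0 × √1.175 = 2.17 in Case A and 2.0 × √1.35 = 2.32 in Case B, taking 8.0 as the total within-cell variance.

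**The case against.** **The size is not known.** The documents contain no ICC. At ICC 0 there is no error, and at 0.01 it is at most about one percentage point. This stands. A reader might infer that the 5% level is certainly lost; the protocol supports only the conditional statement.

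**Some of the grouping is not described.** PD group size is absent. A reader might also assume that session groups are formed by village, or that one fixed facilitator pair stays with one fixed set of caregivers. The text says only that two facilitators lead each workshop and that four are trained. The concern needs neither assumption: joint sessions and joint menus are enough to make correlation plausible.

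**The statistical analysis plan is not shown and could add group terms.** This is fair in part, since the limitations section mentions an adjustment that the analysis section omits. But the protocol names the model and sizes the trial for individual randomization, and nothing in it points to group terms. Followed as written, it ignores the grouping.

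**For PFT there is a larger problem that group terms do not solve.** The Randomization and blinding section says the CURIE clusters form two geographically defined groups, so PFT level coincides with area. With 62 children per area and an assumed between-area variance share of 0.01 to 0.05, R = 1 + 62ρ/(1 − ρ) = 1.63 to 4.26, and the PFT test's error would be about 12% to 34%. A reader might infer that a workshop effect makes the PFT p-value valid. It does not, because area cannot be separated from PFT.

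**Power might seem to settle the matter.** It does not. Power says nothing about whether standard errors are right, and the 64% vs 29% in the sample-size section is malnutrition prevalence, not the weight-gain primary outcome.

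**Conclusion.** The point holds in conditional form. The protocol fixes an independent-errors ANOVA for two group-delivered interventions, so intervals are too narrow and the 5% level is exceeded whenever weight gains correlate positively within session groups. The claim is firmest for PD, which is randomised to individuals within each CURIE arm. Its likely size runs from negligible (ICC 0.01) to a moderate inflation (ICC 0.05-0.10), and it is greater in Case B than in Case A. This rests on an assumed ICC and on applying the 6-10 workshop size to PD. For PFT the grouping adds to a geographic confounding that no group term can remove. The change should be made because it is cheap and because group membership may not be recoverable after delivery.

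**What to change.** 1. Record each child's PD session group and PFT workshop group during delivery, including changes of group.
2. Replace the plain ANOVA with a model containing PD, PFT and PD×PFT that allows for these groups. One option is random group effects in the grouped conditions only (partially nested), with children who attend no group treated as singletons or given their own residual variance. The other is cluster-robust standard errors. Use a small-sample correction in either case.
3. Apply the same group terms to the threshold primary outcome, for example in a mixed or cluster-robust binary model, and to the continuous secondary outcomes. A linear model of weight change alone would not match the primary outcome as defined.
4. State that this does not repair the PFT effect, and report that effect with the limit that PFT is confounded with two geographically defined groups.

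The cost is one extra recorded variable per intervention, a change to the analysis text and slightly wider intervals. With groups of about 8, 62 children make only about eight groups per factor (62/8 = 7.75), so the group variances will be poorly estimated; hence the small-sample correction. The documents do not give what is needed to state the loss of power for the threshold outcome.

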This study will be hinged on the cerebral palsy in Uganda risk factors, intervention and epidemiology (CURIE) research project which has implemented at the Iganga Mayuge health and demographic surveillance sites (IM-HDSS) in eastern Uganda since 2015. The CURIE project conducted the CP prevalence study in 2015 identifying 97 children with CP through a three stage screening process[^9^](#_ENREF_9). Ninety seven age and sex matched controls without CP were also recruited in 2015 for the CURIE follow-up study utilizing the CURIE prevalence study findings as baseline, and later conducting follow-up assessments in 2019. Using similar tools, gross and fine motor function, and nutrition and clinical examination assessments were made at the two points of assessment in 2015 and 2019 among the same study population of children with CP and their matched controls. An intervention study (Akwenda) was there after conducted by the CURIE study team between 2021 and 2022 in which effectiveness of a comprehensive intervention among surviving children with CP was tested. The Akwenda intervention included a Carer-to-Carer approach (parent facilitator trainings) on child functional outcomes, and caregiver quality of life, and a communication and advocacy intervention to improve community perceptions towards CP. The current study will utilize the CURIE intervention study arms to answer its intended objectives while using the same study population.

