**Randomization and blinding:**

**Randomization of participants from the CURIE (Akwenda) intervention study**: Eligible children with CP in the intervention group of the CURIE intervention study will be randomly assigned to receive PFT conditions so as to create the “both PD and PFT”, and “only PFT” conditions, as these individuals will receive PFT by default of the CURIE study. Likewise, participants in the CURIE control group will be randomly assigned to receiving, the “only PD condition”, and the “control” (neither PD nor PFT) condition.

**Randomization of participants from other organisations:** Since not all the CURIE intervention study participants may be eligible to participate (malnourished), other eligible caregivers and their children with CP sampled from elsewhere in the study site will be allocated to either the PFT or control groups of the CURIE study arms based on home village vicinity to make up the required sample for each of the four experimental conditions. Research assistants will be provided with the allocation of all participants after the baseline survey.

In order to avoid contamination, participants in the CURIE-intervention study have been allocated to clusters depending on the village where they reside. Neighboring villages were clustered together to reduce contamination between groups resulting in two geographically defined groups matched for age, sex and motor function. Given the similarity in study sites of the CURIE- study and this study, participants in our study will be allocated based on the already determined CURIE-intervention or control group village clusters as earlier described to avoid contamination. Participants in the control condition will be on waiting list to receive the PFT intervention later owing to the design of the wider CURIE study arrangement.

**Blinding:** Evaluators will be blinded on group allocations so that parent facilitators and caregivers do not report their subjective outcome measures differently. A group of independent outcome assessors (evaluators), not involved in the intervention, will administer the outcome measures after the interventions. These examiners will be blinded to group allocation to avoid reporting bias.

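### Children are allocated in two recruitment streams, but the planned two-way ANOVA names no term for stream and the allocation section does not secure balance of PD within it

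*Protocol*

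**What the plan says.** The protocol's Randomization and blinding section describes allocation under two headings.

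- **CURIE/Akwenda participants.** Children in the CURIE intervention arm are split at random into PFT with PD and PFT alone, "as these individuals will receive PFT by default of the CURIE study". Children in the CURIE control arm are split at random into PD alone and neither.
- **Recruits from other organisations.** The reason for this stream is given first: "Since not all the CURIE intervention study participants may be eligible to participate (malnourished), other eligible caregivers" are brought in from elsewhere in the study area. They "will be allocated to either the PFT or control groups of the CURIE study arms based on home village vicinity", so as to complete the numbers in each of the four conditions. No separate random step to PD is written for them.

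PFT follows one rule in both streams: "participants in our study will be allocated based on the already determined CURIE-intervention or control group village clusters".

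The Data management and analysis section names the model: "A two-way analysis of variance (ANOVA) will be performed to test the independent main effects of PD and PFT", together with the PD by PFT interaction. It names no other term. Study strengths and limitations (8.0) adds that allocation was not completely random and that group differences in some baseline factors were adjusted for. It does not say which factors, or in which model.

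**The concern.** Recruitment source decides by which procedure a child reaches a cell, and it is known before allocation. That makes it a design factor, although the protocol does not call it a stratum. The streams may differ in age, in services received from the organisations that list them, and in earlier exposure to Akwenda, which ran in 2021-2022 and included parent facilitator training (Introduction). Any of these could affect weight gain.

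Two things are at stake. If both streams are spread evenly over the four cells, the stream difference sits in the error term and widens every interval. If outside recruits fill some cells more than others, which a fill-to-quota rule permits, part of the stream difference is counted as an effect of PD or PFT.

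**Working it through.** **1. The plan's own figure.** Sample size estimation gives a CI width of 2.0, error variance 8.0 and contrast coefficients of ±0.5, so the sum of squared coefficients is 4 × 0.25 = 1. Then n = 4 × 8 × 1 × (1.96/2)² = 30.7, rounded up to 31 per cell, and 4 × 31 = 124. The two-proportion calculation (64% v 29%, two-sided 0.05, 80% power, no continuity correction) also gives 31 per arm. The figure of 31 reproduces.

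**2. Size of the second stream.** The CURIE intervention study recruited "to make-up the desired sample size of 90 children with 45 children per arm".
- If all 90 qualified: 124 − 90 = 34 from outside, 34/124 = 27%.
- If 64% qualified (the 2015 cohort prevalence in Sample size estimation): 90 × 0.64 = 57.6; 124 − 57.6 = 66.4, or 54%.

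The second figure carries a 2015 prevalence over to a different pool, so it is indicative. The first is a floor.

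**3. Streams balanced over cells: precision only.** The documents give no stream difference, so d = 0.5 to 1.0 within-stream SD is assumed. With p = 58/124, p(1 − p) = 0.249. The share of variance due to stream is p(1 − p)d² / (1 + p(1 − p)d²).
- d = 0.5: 0.0622/1.0622 = 5.9%. d = 1.0: 0.249/1.249 = 19.9%.
- 80% power without the term corresponds to 1.96 + 0.84 = 2.80 standard errors. With the term: 2.80/√(1 − 0.059) = 2.89, power 82.3%; 2.80/√(1 − 0.199) = 3.13, power 87.9%.

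On the plan's precision scale, take 8.0 as the variance within stream (an assumption) and let D be the stream difference in outcome units. The variance without the term is 8 + q(1 − q)D², where q is the outside share, and the CI width with 31 per cell is 2 × 1.96 × √(variance/31).

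| D | q | Variance | CI width | n per cell for width 2.0 |
|---|---|---|---|---|
| 0 | any | 8.00 | 1.99 | 31 |
| 1 | 0.27 | 8.20 | 2.02 | 32 |
| 1 | 0.50 | 8.25 | 2.02 | 32 |
| 2.83 (1 SD) | 0.27 | 9.58 | 2.18 | 37 |
| 2.83 (1 SD) | 0.50 | 10.00 | 2.23 | 39 |

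There is no bias in this case. In simulation (20,000 runs, 31 per cell, 8 outside recruits in each cell) type I error was about 0.046 at D = 1 and 0.03 at D = 2.83, so the test is conservative.

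**4. Streams unbalanced: bias.** Bias = D × (difference in outside share between the two levels of a factor). Both examples use assumed imbalances.
- Across PFT, 12/31 outside in the PFT cells v 6/31 in the others: the difference is 6/31 = 0.194. For D = 1, 2 and 2.83 the bias in the PFT effect is 0.19, 0.39 and 0.55 units, and simulated type I error is 0.062, 0.100 and 0.135. The PD test stays at or below 0.05, because streams are even across PD in this example.
- Across PD, a difference of 10 of 62: for an assumed stream difference of 0.3, 0.5 or 0.8 kg, the bias in the PD effect is 10/62 × D = 0.05, 0.08 or 0.13 kg.

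The primary outcome is a weight-gain threshold (above 200 g in 12 days, at least 900 g within 3 months), so these mean differences do not translate directly into it.

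**The case against.** The strongest reply is that the protocol does provide for adjustment: section 8.0 says baseline differences were adjusted for, and a covariate list is commonly left to a statistical analysis plan, which is not shown. In part this stands. It would be wrong to infer that stream is ignored; it is merely not named. But the protocol is not silent on the model. It states one without the factor, and the adjustment in 8.0 depends on which differences happen to be observed. A factor that decides how a child is allocated should not wait for that.

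A reader might infer that the streams differ in age because CURIE began in 2015 by "identifying 97 children with CP through a three stage screening process", so that its members would now be at least 6 or 7. The documents do not support that floor: the CURIE pool of 90 also took children from community organisations, and Study population applies the 2-24 year range to Akwenda participants. Earlier exposure is also only indirect. Control families are wait-listed for PFT, so any prior PFT exposure would sit on the PFT side of CURIE alone, and a single stream term would not fully capture such a stream-by-PFT difference.

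A reader might also infer that outside recruits are not randomised to PD. The text writes no such step, but it does not exclude one after placement on a PFT side. If PD is randomised within stream, the expected bias in PD is zero and only precision is at issue.

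Finally, the documented unit for PFT in both streams is the village cluster. A stream term does not address that larger confounding. This is correct, and no such claim is made here.

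**Conclusion.** The point holds as an improvement to the stated method, not as a demonstrated error in the results. Three facts rest on the protocol alone: there are two allocation procedures, at least 34 of 124 children come through the second, and the stated ANOVA has no term for stream. The 54% share rests on applying the 64% prevalence to the 90 CURIE children. The consequences rest on an assumed stream difference: with balance, 82% to 88% power instead of 80% at 0.5 to 1.0 SD; without it, bias equal to the stream difference times the imbalance, in PD or PFT according to where the imbalance falls. Nothing in the allocation section secures balance, but nothing shows that imbalance will occur.

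**What to change.** - **Data management and analysis:** prespecify recruitment stream (CURIE v other organisation) as a fixed factor in the PD by PFT model, for both the intention-to-treat and per-protocol analyses.
- **Study strengths and limitations (8.0):** reconcile the adjustment described there with that model, so that the unadjusted ANOVA and the adjusted main effects no longer stand side by side.
- **Randomization and blinding:** state that PD is drawn at random separately by stream within each PFT side, which also supplies the step not now written for outside recruits.

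The cost is one degree of freedom, a sentence or so in each section, and no new data, since recruitment source is known for every child. The confounding of PFT with village cluster remains and needs separate treatment.
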